## Assessments and outcomes

### Timing of assessments

Participants will be recruited from September 2019 to December 2022. They will be assessed at baseline (pre-randomization), 3, 6, and 12 weeks (end of treatment). Follow-up assessments will take place at 2 weeks, and at 2, 4, 6, 8, 10, and 12 months post treatment.

### Outcome measures

Primary outcome is insomnia severity measured with the Insomnia Severity Index (ISI) [41] after 12 weeks of treatment. The ISI is a 7-item questionnaire scored on a 5-point Likert scale reflecting the severity of both nighttime and daytime aspects of insomnia disorder as perceived by the participant in the last 2 weeks. Total scores range from 0 (no insomnia) to 28 (severe insomnia). A score of ≥ 10 is used to define clinical insomnia [44] .

We will use the Consensus sleep diary [45] for 1 week. Several variables will be calculated from the sleep diary: sleep efficiency (SE; percentage of time slept from the total amount of time spent in bed), sleep onset latency (SOL; time it takes to first fall asleep), number of awakenings (NOA), and total sleep time (TST, total number of hours the participant has slept). All these estimates are registered for 7 nights and for each variable a mean score over 7 days will be calculated.

Fatigue will be assessed with the subscale Fatigue severity of the Checklist Individual Strength (CIS-20), indicating the level of fatigue in the previous 2 weeks, measured with 8 items on a seven-point scale (range 8–56). A score of 35 or higher on the subscale indicates severe fatigue [46].

Anxiety and depression will be assessed with the Hospital Anxiety and Depression Scale (HADS) [47, 48], which has been extensively used in patients with medical conditions. The HADS contains 14 items (7 on depression and 7 on anxiety). A total score (range of 0–21) for each subscale is computed.

Pain severity and impact of pain on functioning will be measured with the 2-item subscale Bodily pain of the Short-Form 36-item Health Survey (SF-36) [49]. A total score is calculated ranging from 0 to 100. Higher scores indicate less pain and less impact of pain on functioning [50].

Impairment of functioning is assessed with the Work and Social Adjustment Scale (WSAS) [51]. The WSAS assesses five domains of functioning (work, home management, social leisure activities, private leisure activities, close relationships) with one item each. Each item is scored on an 8-point Likert scale. The usual timeframe (1 year) is adjusted to the past 2 weeks.

### Treatment evaluation

Adherence to CBT-I is assessed by a 5 item self-constructed questionnaire. This questionnaire assesses on a 5-point scale the extent to which participants followed each of their 6 treatment instructions (e.g., sleep hygiene advices, relaxation, use of sleep diary, sleep restriction and/or stimulus control, worry program and thought diary) since their prior visit. Item scores are added and the range of the total score is between 5 and 25. A higher score represents a better adherence. Furthermore, the number of missed sessions per participant will be tracked.

Treatment adherence to medication will be measured by pill count and a questionnaire (the Medication Adherence Rating Scale (MARS-5) [50] at 12 weeks. The MARS-5, a self-report instrument, contains 5 items regarding medication adherence. Each item is rated on a 5-point Likert scale, and the range of the total score is between 5 and 25. A higher score represents better medication adherence. Adherence by pill count will be calculated by the number of tablets provided minus the number of tablets returned to the investigator or reported as lost divided by the number of days on the study (correcting for dose) multiplied by 100.

Side-effects (including daytime sleepiness) are measured with the Antidepressant Side-Effect Checklist (ASEC) [52], which consists of 21 symptom items scored on a 4-point scale. An additional item asks whether the patient believes this symptom is linked to the treatment. Room for comments and additional side-effects is provided and three additional symptoms are asked. For this study, we split symptom 2 “Drowsiness” into “difficulty waking up/drowsiness when waking up” and “drowsiness during the day.” Symptom 3 “Insomnia” (difficulty sleeping) was split in “vivid dreams” and “disturbed sleep” as these might be side-effects of the treatment. The number, type, and severity of symptoms and their assumed link to treatment will be used to describe the experienced side effects. Daytime sleepiness (as a symptom) is measured by the Epworth Sleepiness Scale (ESS) [53]. The ESS is a 8-item questionnaire (scores 0–24) that requires participants to indicate how likely they would be to fall asleep or doze in various situations. ESS scores > 10 are considered to indicate excessive levels of daytime sleepiness.

For the AM group, withdrawal from medication will be measured with the 43-item Discontinuation-Emergent Signs and Symptoms (DESS) checklist [54], adjusted to self-administration format. Participants will be asked whether they have newly experienced one of the listed signs or symptoms during the first week after they have discontinued the treatment. The number of newly occurring events will be used to measure the effect of discontinuation.

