### Secondary objective

Secondary objectives include to evaluate 1) relapse in insomnia rates in both groups up to 12 months post treatment, 2) secondary outcomes after 12 weeks and 12 months of treatment (sleep quality, fatigue, pain, depression, anxiety, physical functioning, impairment of functioning), 3) treatment evaluation (side-effects, adherence and withdrawal), and 4) possible mediators and moderators of treatment outcome.

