The primary analysis will be conducted according to intention-to-treat, i.e., all randomized patients are included and are analyzed in their randomly assigned treatment group. We will use multiple imputations to handle missing data for outcomes that are based on the measurement at a single time point, including the primary outcome of the ISI score at week 12. We will include all baseline demographic and clinical characteristics in the imputation model. We will impute a total of five datasets and these will be pooled according to Rubin’s rule [63].

Additionally, the mean ISI score over time will be compared between the two treatment groups using linear mixed models with treatment group (amitriptyline or CBT-I) and time (6 and 12 weeks from baseline) included as fixed effects and ISI score at baseline included as covariate.

We will repeat the ANCOVA and the linear mixed models analysis of the ISI score as a per protocol analysis in which only patients who actually received their assigned treatment (in the CBT-I group attendance of at least 5 out of 7 sessions and in the AM group at least 70 out of 84 days medication) will be included.

Percentages responders until relapse at 2, 4, 6, 8, 10, and 12 months post treatment in both treatment groups will be compared using survival analyses. We will express the difference between amitriptyline and CBT-I in effect sizes and percentage responders. Treatment response is defined as ≥ 8 point reduction on ISI. A relapse is defined as a drawback of ≤ 8 points to the baseline score of the Insomnia Severity Index measured during follow-up at two subsequent measurements.

ANCOVA will be repeated on the secondary outcome measures assessed at week 12 and 12 months, adjusted for the baseline measurement and the linear mixed models will be repeated for the secondary outcomes sleep quality, fatigue, emotional complaints, physical functioning, impairment of functioning, and pain, all assessed at weeks 6 and 12 and 12 months post treatment adjusted for the baseline measurement, according to intention to treat and per protocol analyses. Bonferroni corrections will be applied to the p-values to account for multiple comparisons.

Rates of reported side effects, withdrawal, and rebound symptoms as well as the treatment evaluation items will be described.

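### The count of new symptoms after stopping amitriptyline has no comparator, so it cannot be attributed to discontinuation as the wording implies

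*Protocol article*

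**What the plan says.** Under Treatment evaluation, the protocol article assigns the instrument to one arm: "For the AM group, withdrawal from medication will be measured with the 43-item Discontinuation-Emergent Signs and Symptoms (DESS) checklist". Patients complete it themselves and are asked "whether they have newly experienced one of the listed signs or symptoms during the first week after they have discontinued the treatment". The use of the result is then fixed: "The number of newly occurring events will be used to measure the effect of discontinuation".

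The Secondary objective section lists withdrawal as one component of treatment evaluation, beside side-effects and adherence. The Statistical analysis section is more modest about the same data: "Rates of reported side effects, withdrawal, and rebound symptoms as well as the treatment evaluation items will be described". It names no test and no contrast between arms for them.

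Timing of assessments gives a schedule for participants in general, without distinguishing arms: "Follow-up assessments will take place at 2 weeks, and at 2, 4, 6, 8, 10, and 12 months post treatment". The text does not say at which assessment the DESS is completed. The 2-week assessment is the first listed follow-up after the week that the checklist asks about.

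**The concern.** Everyone enrolled has a long-term medical condition or persistent physical complaints (Participants), and other medication, benzodiazepines included, may be used during the trial (Concomitant care during the trial). In such a population a 43-item list will pick up some new symptoms in any week, whether or not a drug has just been stopped. The trial is open label (Randomization and blinding), and the neurologist guides the stop at 12 weeks (Medication), so expectation can also shape what is reported.

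The neighbouring side-effect checklist (ASEC) is used to describe, and it asks patients whether they link a symptom to the treatment. The DESS paragraph mentions no such item, yet it makes the stronger claim of measuring an effect.

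At stake is the reading of a named secondary objective. Background symptoms could be taken for withdrawal, or real withdrawal could be dismissed as background. If CBT-I patients never receive the checklist, a later analysis cannot recover the missing background rate.

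**Working it through.** The plan gives no figure for this measure, so there is nothing of its own to reproduce.

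**Inputs**
- Number of items: 43 (Treatment evaluation).
- Window: the first week after stopping (same section).
- Arms assessed: amitriptyline only (same section).
- Planned analysis: description (Statistical analysis).
- Weekly probability *q* that an item arises newly for unrelated reasons: not in the documents. Assumed range 1% to 5%.

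**Step 1: what the count contains.** Write the expected count in the amitriptyline arm as *B* + *D*. *B* is new symptoms unrelated to stopping. *D* is everything that follows from stopping: withdrawal proper, loss of the drug's benefit, and expectation. The plan observes only the sum. With no second measurement of *B*, neither term can be estimated.

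**Step 2: how large *B* could be.** With no effect of stopping (*D* = 0), the expected count is 43 × *q*. If the items are also independent, the share of patients with at least one new symptom is 1 − (1 − *q*)^43.

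| Assumed *q* | Expected new symptoms | Share with at least one |
|---|---|---|
| 1% | 43 × 0.01 = 0.43 | 1 − 0.99^43 = 35% |
| 2% | 43 × 0.02 = 0.86 | 1 − 0.98^43 = 58% |
| 5% | 43 × 0.05 = 2.15 | 1 − 0.95^43 = 89% |

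The middle column is the relevant one, because the plan uses the number of events. It does not need independence. The last column does, and positively correlated symptoms would lower it.

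**Step 3: what a CBT-I count would add.** Randomisation makes *B* over the same week estimable from the CBT-I arm, so the difference between arms removes new background symptoms. It does not separate the parts of *D*.

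**Step 4: whether the difference would be informative.** Take 84 patients with data per arm (the evaluable number in Sample size), independent items, and SD = √(43 × *q* × (1 − *q*)). The 95% half-width for the difference in mean count is 1.96 × SD × √(2/84).
- *q* = 2%: SD = √(43 × 0.02 × 0.98) = 0.92, half-width 0.28.
- *q* = 5%: SD = √(43 × 0.05 × 0.95) = 1.43, half-width 0.43.

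These are optimistic. Positively correlated symptoms, and CBT-I patients who passed the assessment before the checklist was added, would widen them. Even so, a background of 0.86 or 2.15 could be estimated well enough to be useful.

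**The case against.** The strongest reply is that the planned use is descriptive. The Statistical analysis section promises no test and no causal estimate for withdrawal, so the fault may be one loose phrase. That largely stands. It limits the harm, and it also shows that the two sections should be aligned.

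Second, the checklist asks only for newly experienced symptoms, which is a within-patient reference. It is meant to exclude long-standing complaints, probably the main background in this population. This stands too. What remains is new, unrelated symptoms or flares arising within one week.

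Third, CBT-I patients have no drug to stop and know it. Their answers can supply a background rate, but they cannot remove the expectation of withdrawal symptoms or separate withdrawal from the return of complaints that the drug was relieving. This is correct. The difference would be a background-corrected description and not a clean causal estimate.

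Fourth, the size rests on assumed rates. That is so. It shows only that the background need not be negligible, not what it is.

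Two stronger readings are tempting, and the documents support neither. A reader might infer that the count is worthless and cannot measure anything. It does record new symptoms after stopping, with pre-existing complaints set aside, and it has descriptive value. A reader might also infer that withdrawal belongs to a planned safety comparison with CBT-I, since the Discussion speaks of comparable treatment evaluation. That remark is general and does not name withdrawal or the DESS. The Secondary objective section specifies both groups for relapse but not for withdrawal.

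**Conclusion.** The point holds in a limited form. As the article words it, the amitriptyline-arm count is to measure the effect of discontinuation, but without a comparator it also contains new symptoms unrelated to stopping and cannot be attributed to discontinuation. On an assumed weekly rate of 1% to 5% per item, that background is about 0.4 to 2.2 new symptoms per patient. The range is illustrative, because the documents give no rate.

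The consequence is small. No primary or confirmatory result depends on the DESS, and the Statistical analysis section already treats withdrawal as descriptive. This is a cheap improvement to a named secondary objective.

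**What to change.** 1. Give the same checklist to the CBT-I arm at the existing 2-week post-treatment assessment, worded as symptoms newly experienced in the first week after the end of the 12-week treatment period.
2. Report the count in each arm and the difference with its confidence interval, labelled as a descriptive, background-corrected estimate. Base the difference on patients assessed while both arms were receiving the checklist, so that the comparison stays a randomised one.
3. State with the result that open-label expectation and loss of drug benefit remain in the difference.
4. Align Treatment evaluation with Statistical analysis by wording the amitriptyline count as describing newly reported symptoms after discontinuation. This wording change is worth making even if the checklist is not extended.

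The cost is one extra questionnaire for CBT-I patients. Questionnaires are already collected online, with paper on request (Additional measures), and the assessment already exists. CBT-I patients already past that assessment would lack the data. Trial status reports 68 of 190 participants randomised at submission, so 190 − 68 = 122 were then still to be randomised; the article does not say how many of the 68 had passed the 2-week assessment.

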### Moderators

The Treatment Perception and Preferences (TPP) measure [55] will be used to assess treatment preference and attributes that patients take into consideration when formulating their preferences. Nine items assess the treatment attributes related to each treatment (appropriateness, effectiveness, risks, convenience), which are rated on a 5-point scale (range 0–4). The item measuring risks will be recoded so that higher ratings on all items reflected a favorable perception of the treatment. The items are followed by two questions assessing treatment preference.

Type of insomnia will be assessed with two components of the Insomnia Type Questionnaire (ITQ) [40], namely the Subjective Happiness Scale (SHS) and the Positive And Negative Affect Scale (PANAS). The SHS [56] is a 4-item questionnaire to asses subjective happiness rated on a 7 point scale (range 1–7). Higher scores reflect greater happiness. The PANAS [57] contains 20 items on two subscales that assess a person’s positive and negative trait affect using a 5-point scale (1 = “very slightly or not at all”; 5=” extremely”).

Causal attributions which patients use to explain their insomnia will be assessed using 12 items of the Causal Attributions of my Insomnia questionnaire (CAM-I), developed by Harvey et al. [58]. The items reflect 12 domains that are commonly attributed to contribute to insomnia, such as sleep-related thoughts, bodily arousal, and lifestyle-related factors. Patients are asked the following question: “How likely do you think it is that the following factors contributed to your insomnia?” The domains are rated on a 7-point Likert scale. In this study, 3 domains (medical illness, bodily sensations and side-effects of pharmacological treatment for medical illness) will be added. At the end of the scale, an open-ended question will provide the possibility to list attributions that were not addressed by the modified CAM-I scale.

### Mediators

Dysfunctional beliefs about insomnia will be assessed with the 16-item brief Dysfunctional Belief and Attitudes about Sleep scale (DBAS-16) [59]. The sum of the DBAS score will be averaged so that the total score ranges from 0 (no dysfunctional beliefs) to 10 (severe dysfunctional beliefs).

Sleep-related arousal will be measured with the Pre-Sleep Arousal Scale (PSAS) [60]. The PSAS consists of 16 items that range from 1 (“not at all”) to 5 (“extremely”), higher scores indicating more arousal. Originally, the PSAS consists of two 8-item subscales concerning either cognitive or somatic arousal (*α* = 0.76–0.81). In correspondence with Vincent and Walsh [59], we report in this study on the sum-score of the PSAS.

All of the above questionnaires are freely available or permission for use has been granted by the authors.

### Additional measures

Current and previous use of sleep medication will be assessed by the neurologist-somnologist and registered in the electronic patient file/record. In addition to the self-report questionnaires, we will gather data on consultations (frequency of and reason for consultation, diagnoses on somatic and mental health) and prescription of medication from the electronic patient file during the year before and the year following the randomization.

Patient characteristics (i.e., sex, age, BMI, marital status, highest attained educational level, current work status, smoking status, alcohol consumption, duration of insomnia), life events in the past year, and additional means to improve sleep (e.g., vitamin preparation) are assessed in a self-constructed questionnaire.

Data will be collected and stored digitally using a structural database (CastorEDC). This database takes safety measures for collecting, storing, and processing data to ensure strict confidence and avoid disclosure of data to any third party without permission of the user. This system allows no missing items and sends reminders automatically. In case participants prefer a paper version of the questionnaires, this will be sent by regular mail and the filled in forms will be stored safely.

A diagrammatic representation of the trial process (enrolment, intervention and assessment) is shown in the Standard Protocol Items: Recommendations for Interventions (SPIRIT) diagram (Fig. 2). For the full SPIRIT checklist, please see supplementary material Additional file 1.

**Fig. 2 Fig2:**
[figure not shown]
SPIRIT diagram

### Sample size

We hypothesize that the effect of low-dose AM at 12 weeks is non-inferior to the golden standard CBT-I. A low-dose AM will be considered non-inferior to CBT if the mean post treatment ISI total score does not exceed that of the CBT-I group by more than 4 points, i.e., 50% of the minimum clinical significant difference reported following CBT-I. The standard deviation of the ISI in our study is assumed 4.4 [61]. Sample size determination following the recommendations outlined in Tamayo-Sarver et al. [62] using a one-tailed test and a 5% significance level showed that 84 participants in each group will provide adequate power (90%) to reject the null hypothesis that the ISI change produced by low-dose amitriptyline is not similar to those produced by CBT-I. The dropout rate is estimated to be 13% [41]. Hence, 190 participants in total will be included.

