### Statistical analysis

Demographic and clinical characteristics (e.g., age, gender, medical condition, preference and type of insomnia) and primary and secondary outcomes at baseline (e.g., sleep efficiency, emotional complaints) will be presented in means (standard deviations) and numbers (percentages) depending on their distribution.

The null hypothesis states that there is a difference in mean scores on the primary outcome between the treatment groups; the alternative hypothesis is that the difference in mean scores on the primary outcome measure does not differ by more than the non-inferiority margin. The primary analysis will be conducted according to intention-to-treat, i.e., all randomized patients are included and are analyzed in their randomly assigned treatment group. Outcomes that are based on measurements at multiple time points, i.e., weeks 6 and 12, are analyzed using mixed linear models. Mixed linear models can handle the presence of missing data without the need for imputation and still provide valid estimates of treatment effects.

The primary outcome for analysis is the mean subjective insomnia severity as assessed using the ISI at week 12. To test for the difference between the two treatment groups, the primary outcome of ISI score at week 12 will be analyzed using analysis of covariance (ANCOVA) with treatment group (amitriptyline or CBT-I) as the independent variable and the baseline value as a covariate. We will check for violations of necessary assumptions of ANCOVA (normality, homogeneity of variance and random independent samples). We will calculate a one-sided 95% confidence interval around the mean difference in the primary outcome between the treatment groups to determine if the upper limit of the confidence interval will be below the non-inferiority margin of 4 points. Amitriptyline will be declared non-inferior to CBT-I if the upper bound of the 95% confidence interval does not exceed the non-inferiority margin of 4 points. If amitriptyline is shown to be non-inferior, we then will proceed to superiority hypothesis testing. For superiority testing, we will consider the two sided 95% confidence interval of the mean difference between both groups on the primary outcome as established in the ANCOVA and verify if it includes zero or not.

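### The stated 84 per group for 90% power does not follow from the printed margin (4), SD (4.4) and one-sided 5% test; an assumption behind the 84 is missing or misstated

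*Protocol article*

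**What the plan says.** The Sample size section calls amitriptyline non-inferior if its mean ISI after treatment "does not exceed that of the CBT-I group by more than 4 points, i.e., 50% of the minimum clinical significant difference reported following CBT-I". It adds: "The standard deviation of the ISI in our study is assumed 4.4". From these it reports that a calculation "using a one-tailed test and a 5% significance level showed that 84 participants in each group will provide adequate power (90"%). The total of 190 is then reached with 13% dropout.

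The Statistical analysis section applies the same margin at the same level. It plans as follows: "We will calculate a one-sided 95% confidence interval around the mean difference in the primary outcome between the treatment groups". Amitriptyline is declared non-inferior "if the upper bound of the 95% confidence interval does not exceed the non-inferiority margin of 4 points".

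Neither section gives the true difference between the arms that was assumed when the trial was sized.

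**The concern.** Margin, SD, significance level, sidedness, power and group size are printed together as one justification, so a reader can recompute it. With equal true means, the group size is about four times what the other figures call for. Required size varies with the inverse square of the distance to be detected, so a factor of four corresponds to a distance of half the stated margin, or to twice the stated SD.

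The possible explanations mean different things for the trial. If amitriptyline was assumed to be 2 points worse, the trial was sized in the expectation of a deficit that readers are not told about. If the SD was taken as about 8.8, the printed 4.4 is not the value used. If a 2-point margin was used for planning, the decision rule is twice as wide as the design. The margin and the size justification carry the single primary claim, and an explanation offered after the results are known would persuade few readers.

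**Working it through.** **Inputs.** Margin 4, SD 4.4, one-sided 5%, power 90% and 84 per group come from the Sample size section; 1:1 allocation comes from the opening of Methods/design. The true difference is not stated. It is taken as 0 as an assumption, and other values are shown below.

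**Attempt to reproduce the plan's figure.** For non-inferiority of two means,

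n per group = 2 × (z₀.₉₅ + z₀.₉₀)² × SD² / d², where d is the margin minus the true difference.

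With z₀.₉₅ = 1.645 and z₀.₉₀ = 1.282, the squared sum is 8.564 (unrounded z values).

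- d = 4: 2 × 8.564 × 19.36 / 16 = 20.7, so 21 per group; the exact noncentral t gives 22. The plan's 84 is not reproduced.

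**Method variants with margin 4, SD 4.4 and true difference 0** (exact t unless noted):

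| Variant | n per group |
|---|---|
| One-sided 2.5%, 90% power | 27 |
| One-sided 5%, 95% power | 27 |
| One-sided 2.5%, 95% power | 33 |
| Equivalence (two one-sided tests), 5%, 90% power | 27 (normal; 26.2 unrounded) |

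None is near 84.

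**What does give 84.**

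- d = 2 with SD 4.4: 2 × 8.564 × 19.36 / 4 = 82.9, so 83; the exact t gives 84. This covers both a 4-point margin with amitriptyline truly 2 points worse and a 2-point margin with no difference.
- d = 4 with SD 8.8: the ratio SD/d is the same, so the result is again 82.9 (normal) and 84 (exact t).

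Solving backwards from 84 by the normal formula gives d = 1.99 at SD 4.4, or SD = 8.86 at d = 4.

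**What 84 per group delivers under the 4-point rule at SD 4.4.** The standard error is 4.4 × √(2/84) = 0.679.

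| True deficit of amitriptyline | Probability of declaring non-inferiority |
|---|---|
| 0 | above 99.9% |
| 1 point | 99.7% |
| 2 points | 90% |
| 2.9 points | about 49% |

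The largest observed deficit that passes is about 4 − 1.645 × 0.679 = 2.9 points. Under a 2-point rule it would be about 2 − 1.117 = 0.9 points. With SD 6, power at zero difference is still 99.6%.

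**Dropout step.** 2 × 84 = 168, and 168 × 1.13 = 189.8, hence 190. The 84 was therefore carried forward as a per-group figure, and the discrepancy lies in the 84 itself.

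**The case against.** The strongest reply is that the article does not print every input. A non-inferiority calculation needs an assumed true difference, and none is given. With an assumed 2-point deficit for amitriptyline, the margin of 4, the SD of 4.4, the 84 and the 90% all agree by exact t. On that reading nothing was miscalculated; one assumption went unreported. The article condenses a fuller protocol and relies on a cited method, and neither is shown. This stands: the document cannot settle whether 84 is an error or an incompletely reported calculation.

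A reader might go further and infer that the trial was planned on a 2-point margin and that the decision rule was later widened to 4. The document does not support that. Four points appears consistently in the Sample size and Statistical analysis sections. It is described as half of the minimum clinically significant difference, which implies 8 points, and 8 points is also the response threshold under Statistical analysis. A 2-point margin is mentioned nowhere; it is only one of several ways to arrive at 84. Another keeps the 4-point margin: a change-score SD of 4.4 × √2 = 6.22 gives 41.4, so 42 per group by the normal formula, which is 84 in total (43 per group by exact t). A total printed as a per-group figure would still be an error, but not in the margin.

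The reply is also right about harm. The trial is not underpowered for its rule, the type I error at a true 4-point deficit stays at 5%, and the rule can be applied as written. The high chance of passing a drug that is truly 2 points worse is a property of the 4-point margin at this size; it does not make the rule invalid.

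What does not fall away is that the 90% claim cannot be obtained from what is printed under the usual default of no true difference.

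**Conclusion.** The point holds as a defect in the sample-size statement. With zero true difference, the printed inputs need 21 to 22 per group, and 84 per group gives power above 99.9%, not 90%. The combination of 84 and 90% requires something the article does not state: with the other inputs as printed, a 2-point distance between margin and true difference, or an SD of about 8.8. The article does not identify which. It gives no ground for saying that the decision margin was altered or that the calculation and the decision rule necessarily use different margins.

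This rests on the stated SD, level and allocation, on a two-sample comparison of means, and on the assumption of no true difference where none is given. Because the defect concerns the justification of the one primary claim and costs little to correct, it should be settled before analysis, although neither power nor type I error for the 4-point rule is at risk.

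**What to change.** Before the data are analysed, keep the 4-point margin in both sections and correct the sample-size statement in one of two ways:

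- State the assumed true difference or the SD under which 84 per group gives 90% power, with a reason for it.
- Or replace 90% with the actual power at 84 per group, margin 4 and SD 4.4: above 99.9% with no true difference, and about 90% if amitriptyline is truly 2 points worse.

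The sponsor should check the source calculation first. If it shows that a margin other than 4 was used, the Sample size and Statistical analysis sections should be reconciled by a dated amendment before analysis.

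The cost is a wording correction or, at most, a short amendment. No extra patients are needed, and the planned analysis does not change unless the source calculation shows a different margin.

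### The stated 84 per group and 90% power do not follow from the stated 4-point margin, SD of 4.4 and one-sided 5% test, and the protocol does not say which input differs

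*Protocol article*

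**What the plan says.** The Sample size section of the protocol article gives nearly all the inputs. Amitriptyline counts as non-inferior if its mean post-treatment ISI score "does not exceed that of the CBT-I group by more than 4 points", and the 4 points are described as "50% of the minimum clinical significant difference reported following CBT-I". On variability: "The standard deviation of the ISI in our study is assumed 4.4". The test is one-tailed at 5%, and the section concludes that "84 participants in each group will provide adequate power (90%) to reject the null hypothesis". No assumed true difference between the arms is given. Dropout is put at 13%, and the section ends: "Hence, 190 participants in total will be included".

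The Statistical analysis section uses the same margin for the decision. It calculates a one-sided 95% confidence interval from an ANCOVA adjusted for baseline, and declares non-inferiority "if the upper bound of the 95% confidence interval does not exceed the non-inferiority margin of 4 points". If that succeeds, the two-sided 95% interval is examined to see whether it includes zero.

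**The concern.** A margin of 4 points against an SD of 4.4 is 4/4.4 = 0.91 SD. A shift that large is detected with about 20 patients per arm, so 84 for 90% power is about four times too many. Required n varies with the square of SD divided by (margin minus true difference). A fourfold gap therefore points to a factor of two in one of those quantities.

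At stake is what the trial's main conclusion means. If the decision rule and the sample size rest on different inputs, the power statement is wrong, or the margin is not the one used for sizing, or an assumption has been left out. An observed deficit of, say, 2 points would then be non-inferior or not depending on which input is believed, and that cannot be settled credibly once results by arm are known.

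**Working it through.** **Inputs.** Margin 4, SD 4.4, one-sided alpha 0.05 (z = 1.645), power 90% (z = 1.282), 84 per group, dropout 13% and total 190 come from Sample size; 1:1 allocation comes from Methods/design. True difference 0 is my assumption, because none is stated.

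**Attempt to reproduce the plan's figure.** n per group = 2 × (1.645 + 1.282)² × (SD / (margin − true difference))².

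- As stated: 2 × 8.567 × (4.4/4)² = 20.7, so 21 per group; 22 with the t distribution. The stated 84 is not reproduced.
- Power at 84 per group: SE = 4.4 × √(2/84) = 0.679. Then 4/0.679 − 1.645 = 4.25, giving power of 99.999%.

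**Variants at margin 4, 90% power.**

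| Variant | n per group |
|---|---|
| One-sided 2.5% | 26 (normal), 27 (t) |
| Equivalence (two one-sided tests), alpha 0.05 | 27 |
| Equivalence (two one-sided tests), alpha 0.025 | 32 |
| SD × √2, as for a change score | 42 |

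None comes near 84. Baseline adjustment by ANCOVA would only lower the requirement.

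**What does give 84 and 90%.**

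- Margin minus true difference = 2: 2 × 8.567 × (4.4/2)² = 82.9, so 83 (normal) or 84 (t). Power at 84 is 90.3% (normal) or 90.1% (t). A 2-point margin with no difference, and a 4-point margin with a true deficit of 2, give the same result.
- Margin 4, no difference, larger SD: SD = 4 / (2.927 × √(2/84)) = 8.86, about twice the stated 4.4.

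**What the decision rule does with 84 per group (SD 4.4).**

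- Largest observed deficit that passes at margin 4: 4 − 1.654 × 0.679 = 2.88 points.
- Smallest deficit significant at two-sided 5%: about 1.34 points (t; 1.33 by the normal formula).
- Deficits from about 1.34 to 2.88 are therefore both non-inferior and significantly worse. At 2.88 the lower two-sided 95% limit is 1.55 (normal).
- At margin 2 the largest passing deficit would be about 0.88, so results between 0.88 and 2.88 depend on which margin applies.

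**How often non-inferior and significantly worse coincide at margin 4.** The true deficits below are assumptions, since the document gives none.

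| True deficit | Declared non-inferior | Non-inferior and significantly worse |
|---|---|---|
| 0 | >99.99% | about 2% |
| 1 | 99.7% | 31% |
| 2 | 90% | 74% |
| 3 | 43% | 42% |
| 4 | 5% | n/a: declaring at all is the 5% error |

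**Dropout.** 168 × 1.13 = 189.8, which gives the stated 190. Allowing for 13% loss would be 168/0.87 = 193.1, or 194 in total (97 per group). Recruiting 190 leaves 190 × 0.87 = 165.3.

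**The case against.** The strongest reply is that the 4-point margin is the consistent element. It stands in Sample size and again in the decision rule, and it is half of 8 points, the figure that Statistical analysis uses to define response. No 2-point margin appears anywhere. On this view the power statement is the outlier, the trial is simply over-powered, and the error rate at a true deficit of 4 remains 5%. This stands, and it limits what can be concluded.

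A reader might infer that the trial was really sized for a 2-point margin. The documents do not support that: an unstated expected deficit of 2 points, or an SD near 8.9, gives the same n, and the cited sizing method is not shown. A reader might also call a pass at a true deficit of 2 points a false claim. That presupposes the 2-point margin; under the stated rule such a deficit lies inside the margin. Non-inferiority and a significant difference can coexist in any precise non-inferiority trial, and here the frequency depends strongly on the unknown true difference. Finally, whether 4 points is too wide relative to CBT-I's effect over control cannot be judged, because the document gives no such effect on the ISI.

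The reply does not remove the contradiction. Every explanation requires a number in Sample size to be changed or added.

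**Conclusion.** The stated n and power do not follow from the stated inputs: 21 to 22 per group are needed where 84 are given, and 84 per group yields more than 99.99% power rather than 90%. This rests on a true difference of 0. The source of the mismatch cannot be identified from the document. The error is not one of too few patients for the stated margin, and type I error at that margin is intact. The consequence lies in interpretation: observed deficits of about 0.88 to 2.88 points change verdict between margins of 4 and 2, and under the stated rule a non-inferiority claim can accompany a significant result in favour of CBT-I.

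The dropout slip is real but minor. About 165 evaluable instead of 168 leaves power above 99.99% at margin 4 with no true difference, and at 89.7% if margin minus true difference is 2.

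**What to change.** Before any look at outcomes by arm, reconcile margin, SD, assumed true difference, power and n in Sample size and Statistical analysis.

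- If 4 points with no true difference is intended, restate the power for 84 per group as above 99.9%, noting that 22 per group would give 90%. Report the two-sided 95% interval with any non-inferiority claim, and say whether it excludes zero in favour of CBT-I. The plan already calculates this interval for its superiority step.
- If a smaller margin, a non-zero expected difference or a larger SD was used for sizing, state it and make the decision rule agree.
- Restate the evaluable number as about 165 from 190 recruited.

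The cost is a short amendment and no extra patients. Timing matters most: Trial status reports 68 randomized at submission, and the correction carries weight only if made before results by arm are seen.
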